### 2.9. Sample size and recruitment assumptions

DREAMER uses a pragmatic recruitment target based on expected RSWA frequency and feasibility within participating centers. Previous quantitative work in adults without RBD showed that isolated RSWA elevations may be detected in a substantial minority of individuals, with approximately 14% of patients without dream-enactment behavior reaching previously established RBD-level RSWA thresholds [4,7]. Therefore, the initial recruitment target is > 500 participants over 18 months, expected to yield approximately 85 individuals with isolated RSWA. Because the DREAMER population is restricted to adults aged ≥40 years, and because RSWA becomes more frequent with age, the number of isolated RSWA cases may exceed this estimate.

The initial 24-month phase is not designed as a definitive phenoconversion trial. Instead, it is designed to assemble an enriched cohort and collect the standardized baseline data required for adequately powered follow-up. Recruitment assumptions will be reassessed after the first 6 months of enrollment. If the observed frequency of isolated RSWA or the rate of technically classifiable vPSG recordings is lower than expected, recruitment targets may be increased, and the comparator strategy may be adjusted by selecting an age- and sex-matched subgroup without RSWA for long-term follow-up.

Assuming approximately 85 participants with isolated RSWA and long-term follow-up over 5 years, the study may observe a sufficient number of incident RBD events to generate preliminary estimates of relative risk compared with participants without RSWA. These estimates will be used to plan future prevention or neuroprotection trials rather than to support immediate clinical implementation.

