### 2.11. Statistical analysis plan

Baseline characteristics will be summarized for the overall cohort and stratified by RSWA status. Continuous variables will be reported as mean and standard deviation or median and interquartile range, according to distribution. Categorical variables will be reported as counts and percentages.

Participants with isolated RSWA will be compared with participants without RSWA. Continuous variables will be analyzed using Student’s t test or Mann-Whitney U test, as appropriate. Categorical variables will be analyzed using chi-square or Fisher’s exact tests. Effect sizes and confidence intervals will be reported whenever possible to avoid overreliance on significance testing.

RAI will be analyzed both as a continuous variable and as a categorical classification variable. Multiple linear regression will evaluate associations between RAI and clinical, pharmacological, sleep, and neurophysiological predictors. Logistic regression will evaluate predictors of isolated RSWA status. Candidate covariates will include age, sex, antidepressant exposure, neurological comorbidity, sleep apnea severity, REM sleep duration, and participating center.

For long-term follow-up, cumulative incidence of RBD will be described using Kaplan-Meier methods. Cox proportional hazards models will estimate the association between baseline isolated RSWA and incident RBD, adjusted for age, sex, medication exposure, center, and relevant sleep-disorder comorbidities. Competing-risk methods may be considered for incident neurodegenerative outcomes or death. Sensitivity analyses will evaluate the influence of antidepressant exposure, minimum REM duration, comorbid sleep apnea, and alternative RAI thresholds.

The extent and pattern of missing data will be reported. If missingness is limited, complete-case analyses will be used. If missingness is substantial and plausibly missing at random, multiple imputation may be considered for regression models. Follow-up attrition will be summarized and compared between RSWA and non-RSWA groups.

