### 2.12. Study status and timeline

The DREAMER study was registered at ClinicalTrials.gov before completion of recruitment. Ethics approval was obtained on 24 January 2024, and participant recruitment started on 22 February 2024. At the time of submission of this Study Protocol, participant recruitment is still ongoing and has not yet been completed, although the recruitment phase is close to completion. Recruitment is expected to be completed by 30 June 2026.

Completion of participant recruitment will be followed by baseline data verification, RAI computation, classification of participants according to the predefined RSWA/RAI criteria, identification of the isolated RSWA subgroup, and selection of the comparator group without RSWA according to the prespecified matching strategy. Therefore, the analytical cohort has not yet been constituted, and no study results have yet been generated, analyzed, or reported.

After completion of recruitment, baseline data validation, and analytical cohort constitution, the longitudinal follow-up phase will begin and will continue for 5 years. Follow-up data collection is expected to be completed approximately by 30 June 2031. Baseline descriptive and feasibility results are expected only after completion of recruitment, database verification, RAI-based classification, comparator-group selection, and database lock, approximately by September–December 2026. Final longitudinal analyses of incident REM sleep behavior disorder and neurodegenerative outcomes are expected after completion of the planned 5-year follow-up period, approximately by late 2031 or early 2032.

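### The plan names Student's pooled-variance t test for a baseline comparison that may be about 85 versus 415; Welch's test would protect against unequal spread at almost no cost

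*Protocol article*

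**What the plan says.** Section 2.11 sets out the baseline group comparison: "Participants with isolated RSWA will be compared with participants without RSWA". For continuous variables it names Student's "t test or Mann-Whitney U test, as appropriate". It gives no rule for unequal variances and does not mention Welch's version. The only nearby criterion is the shape of the distribution, which decides between mean and median summaries. The section also asks for effect sizes and confidence intervals, so that readers do not lean on p values alone.

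On group sizes, section 2.9 states that "the initial recruitment target is > 500 participants over 18 months, expected to yield approximately 85 individuals with isolated RSWA". The size of the group without RSWA is given nowhere. Section 2.9 adds that, if recruitment disappoints, "the comparator strategy may be adjusted by selecting an age- and sex-matched subgroup without RSWA for long-term follow-up". Section 2.12 lists, among the steps before baseline results, "selection of the comparator group without RSWA according to the prespecified matching strategy". No matching ratio is stated.

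The comparison serves the second of the secondary objectives in section 2.1.

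**The concern.** Student's test estimates one common variance. When one group is about five times the other, the larger group dominates that estimate, while the true uncertainty of the mean difference comes mostly from the smaller group. If the two spreads differ, the standard error is therefore wrong, and a larger total sample at the same ratio does not cure it. If the small group is the more variable one, p values are too small and intervals too short. If it is the less variable one, the test is conservative and intervals are too long.

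The emphasis on confidence intervals is no safeguard, because an interval built on the pooled standard error carries the same fault. The alternative test is not a remedy either: Mann-Whitney is chosen for distribution shape and also responds to differences in spread when group sizes are unequal. At stake is the reliability of many unadjusted baseline contrasts, not the primary objective.

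**Working it through.** **Inputs from the document.** Target above 500 and about 85 with isolated RSWA (section 2.9); Student's test named (section 2.11).

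**Inferred.** Comparator 500 − 85 = 415, if all other participants are used.

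**Assumed, because not given.** Two-sided 5% level, normal data, independent groups, and a ratio *r* of the RSWA to the non-RSWA standard deviation between 0.67 and 2.

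**The plan's own figure.** Section 2.9 rests on "approximately 14% of patients without dream-enactment behavior reaching previously established RBD-level RSWA thresholds". At 500 participants that gives 500 × 0.14 = 70, not 85; 85 needs 85 / 0.14 = 607 participants, or 85 / 500 = 17%. The stated 85 is used below, and the other two splits are checked at the end.

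**Formula.** Set the non-RSWA standard deviation to 1.

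- True variance of the mean difference: *r*²/85 + 1/415.
- What Student's test estimates on average: [(84*r*² + 414)/498] × (1/85 + 1/415).
- Approximate actual error: 2 × P(Z > 1.965 × √(estimated/true)).

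**At *r* = 1.5.** True variance = 2.25/85 + 1/415 = 0.02888. Pooled variance = (189 + 414)/498 = 1.2108; times 0.014174 gives 0.01716. The ratio is 0.594, with square root 0.771, so the standard error is about 23% too small. The test then has an effective cut-off of 1.965 × 0.771 = 1.515, and an error of about 13.0%. Simulation gives 13.1%, so a nominal 95% interval covers about 86.9%.

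**At *r* = 0.67.** True variance 0.00769, estimated 0.01286, square root of the ratio 1.293. The standard error is about 29% too large and the error about 1.1% (1.2% in simulation).

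**Simulated type I error, 100,000 data sets per setting:**

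| *r* | Student, 85 v 415 | Welch, 85 v 415 | Student, 85 v 170 | Student, 85 v 85 |
|---|---|---|---|---|
| 0.67 | 1.2% | 5.0% | 2.6% | 5.1% |
| 0.8 | 2.3% | 5.0% | 3.5% | 5.1% |
| 1.0 | 5.0% | 5.0% | 5.1% | 5.1% |
| 1.25 | 9.0% | 5.0% | 6.9% | 5.0% |
| 1.5 | 13.1% | 5.1% | 8.6% | 5.1% |
| 2.0 | 19.6% | 5.1% | 11.1% | 4.9% |

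**Other splits.** At *r* = 1.5, Student's error is 14.2% at 70 v 430 and 14.0% at 85 v 522, so the discrepancy over 85 does not change the conclusion.

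**Mann-Whitney, 85 v 415, spread alone differing (8,000 data sets).** 6.9%, 8.7% and 11.0% at *r* = 1.25, 1.5 and 2.

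**Price of Welch when variances are equal (20,000 data sets, 85 v 415).** Power 70.4% against 70.8% at a standardised difference of 0.30, and 83.1% against 83.5% at 0.35.

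**The case against.** The strongest reply is that the 1:5 comparison may never be run. The figure of 415 does not appear in the article. Section 2.12 places selection of a matched comparator before baseline results. Section 2.6 speaks of a suitable comparison group for TMS and matched comparators for BAEPs, and Table 2 makes the ancillary tests a priority only in the RSWA subgroup. With equal groups there is no distortion. This stands as a limit on scope, especially for TMS and BAEPs. It does not dispose of the point: section 2.9 raises a matched subgroup only as a possible adjustment for follow-up, no ratio is fixed, and neither section 2.11 nor the objective in section 2.1 confines the baseline comparison to a matched subset.

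A second reply is that unequal spread is not shown. That is right. A reader might infer from the Discussion, which calls isolated RSWA potentially heterogeneous, that this group must have the larger standard deviations. The Discussion lists varied causes; it says nothing about the spread of any measured variable, and the comparators are themselves a mixed sleep-clinic population (section 2.4). Nor can one say that the planned intervals are too narrow: they would be too wide if the RSWA group were the less variable.

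Third, an article condenses a fuller plan, and the choice of test variant can be left there. But this is a named test, not an omitted detail. It is true that medication exposures are largely categorical and so fall outside the t test, that no significance level is stated, and that adjusted regressions are planned as well. These facts keep the point small.

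**Conclusion.** The point holds conditionally. If the baseline comparison uses all participants without RSWA, Student's test has an actual error between about 1.2% and 20% for standard deviation ratios from 0.67 to 2, and its intervals are wrong to match. Those ratios, the 5% level, normality and the comparator of 415 are assumptions. The article does not support a claim that error rates in this study will be inflated; it supports only the statement that the named test offers no protection if the spreads differ, in whichever direction. With 85 against 170 the effect is smaller, and with equal groups it disappears. The comparisons are unadjusted and serve a secondary objective, so the consequence is minor. The change is still worth making, because Welch's test keeps its level in every setting examined.

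**What to change.** In section 2.11, replace Student's t test with Welch's unequal-variance t test, and report each mean difference with its Welch confidence interval. It would help to state in the same place whether the baseline comparisons use all participants without RSWA or the matched subgroup, since that decides how much the choice matters. If Mann-Whitney is kept for skewed variables, its result should be read as a difference between distributions, not specifically in location; the change of t test does not alter that.

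The cost is a few words and about 0.4 percentage points of power if the variances are in fact equal. Section 2.12 reports that the analytical cohort has not been formed and nothing has been analysed, so the change can be made before any results are seen.

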### 2.6. Ancillary neurophysiological and biomarker assessments

DREAMER incorporates ancillary assessments to generate mechanistic and trial-readiness information beyond vPSG [17].

The coordinating center will perform transcranial magnetic stimulation (TMS) in participants with isolated RSWA and in an appropriate comparison group without RSWA. TMS will assess cortical excitability and inhibitory/facilitatory intracortical mechanisms. The aim is to determine whether isolated RSWA is associated with early cortical neurophysiological changes analogous to those described in RBD or early synucleinopathy [18].

The Cagliari center will perform cervical, masseter, and ocular vestibular-evoked myogenic potentials when feasible. These measures provide information on brainstem pathways that may be relevant to REM atonia regulation and early RBD-related neurophysiology [19]. Startle response assessment may also be included according to the final harmonized protocol.

The Bologna and San Raffaele centers will perform brainstem auditory evoked potentials in selected participants with isolated RSWA and matched comparators without RSWA. These measures will complement other neurophysiological assessments of brainstem function.

Blood samples will be obtained whenever possible, with priority given to participants with isolated RSWA. Samples will be processed and stored for future proteomic, metabolomic, and glycomic analyses. The purpose is to determine whether isolated RSWA is associated with peripheral molecular signatures overlapping with those previously described in isolated RBD [20,21].

Brain magnetic resonance imaging, computed tomography, dopamine transporter imaging, or other investigations will not be mandated by the protocol, but may be performed when clinically indicated as part of routine diagnostic work-up. Results will be recorded in the eCRF when available.

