### 2.7. Outcomes

The main outcomes of the 24-month cohort-construction phase are:

Number of participants screened, eligible, enrolled, and classifiable by RAI.Frequency of isolated RSWA among enrolled participants.Completeness and quality of vPSG, clinical, neurophysiological, and biosample data.Feasibility of harmonized multicenter eCRF-based data capture.Recruitment rate and retention readiness for long-term follow-up.

The primary long-term clinical outcome is incident RBD, defined by development of clinical dream-enactment behavior with vPSG evidence of RSWA according to accepted diagnostic criteria.

Secondary long-term outcomes include:

Change in RAI over time, when repeat vPSG is available.Development of subthreshold dream-enactment behavior or increased RBD questionnaire scores.Diagnosis of Parkinson disease, dementia with Lewy bodies, multiple system atrophy, or other neurodegenerative disorders.Association between baseline RAI and neurophysiological markers.Association between baseline RAI and blood-based proteomic/metabolomic/glycomic signatures.Attrition, loss to follow-up, and feasibility of repeated annual assessment.

The procedures used to identify and confirm these outcomes during follow-up are described below.

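### The regression of RAI on neurophysiological tests is fitted in people chosen for testing by their RAI, which biases the slope; if testing is local, no model can hold tests from different centers

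*Protocol article*

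**What the plan says.** All places are in the protocol article.

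- **Model (2.11).** "Multiple linear regression will evaluate associations between RAI and clinical, pharmacological, sleep, and neurophysiological predictors". RAI is the dependent variable. Participating center is one of the candidate covariates. Whether the tests enter together or separately is not said. A logistic model for isolated-RSWA status is also planned.
- **Who performs which test (2.6).** "The coordinating center will perform transcranial magnetic stimulation (TMS) in participants with isolated RSWA and in an appropriate comparison group without RSWA". "The Cagliari center will perform cervical, masseter, and ocular vestibular-evoked myogenic potentials when feasible". "The Bologna and San Raffaele centers will perform brainstem auditory evoked potentials in selected participants with isolated RSWA and matched comparators without RSWA".
- **Who is due each test (Table 2 in 2.2).** TMS, VEMPs/startle and BAEPs are each listed for all enrolled participants where feasible, and with priority in the isolated-RSWA subgroup. No row is limited to a center.
- **Centers (2.3).** All four recruit. No section provides for testing a participant at another center.
- **Missing data (2.11).** Complete cases are used if missingness is limited. Otherwise: "If missingness is substantial and plausibly missing at random, multiple imputation may be considered for regression models". Tests not done by design are not treated separately.
- **Use of the results.** The third secondary objective (2.1) relates RAI to clinical and instrumental markers. Section 2.7 lists the association of baseline RAI with neurophysiological markers as an outcome.

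**The concern.** There are two difficulties, one certain in kind and one conditional.

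**Selection on the outcome.** Isolated RSWA is defined by RAI below 0.85. Giving that group priority for testing means that having a test result depends on RAI. A linear regression with RAI on the left-hand side is then fitted in a sample in which low RAI is over-represented, and its slope is not the slope in the cohort. Modelling one test at a time does not cure this.

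**Tests split by center.** If participants are tested where they are recruited, nobody has results from two centers' tests. A model containing, say, TMS and VEMPs would have no one to fit it on, and any estimate would come from the imputation model.

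At stake is the neurophysiological part of the third secondary objective: an overstated association where one exists, or a joint coefficient that the data cannot determine. The pooled clinical, pharmacological and sleep regressions are not affected.

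**Working it through.** **Inputs.** Sections 2.6 and 2.3 give the allocation of tests and the four recruiting centers. Section 2.9 gives a 14% frequency, a target above 500 and about 85 cases. Since 0.14 × 500 = 70 and 85/500 = 17%, I use 14% and 17% as the range for the case rate. The plan gives no figure for the regression itself, so there is none to reproduce.

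**1. Bias from selection on RAI.** Assumptions (mine): RAI (Y) and the marker (X) are standardized and jointly normal with slope ρ = 0.30; cases are the lowest fraction p of RAI; all cases are tested, plus one random non-case each.

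Selection depends on Y only, so X given Y is unchanged: X = ρY + e, Var(e) = 1 − ρ². If v is the variance of Y among those tested:

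- slope of X on Y = ρ, unchanged;
- slope of Y on X = ρv / (1 − ρ² + ρ²v).

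With z the cut-off in SD units and φ the normal density at z, cases have mean −φ/p and mean square 1 + zφ/p. Non-cases have mean φ/(1−p) and mean square 1 − zφ/(1−p).

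| | p = 14% | p = 17% |
|---|---|---|
| z; φ | 1.080; 0.223 | 0.954; 0.253 |
| Cases: mean; mean square | −1.590; 2.718 | −1.489; 2.420 |
| Non-cases: mean; mean square | 0.259; 0.720 | 0.305; 0.709 |
| 1:1 mix: mean; mean square | −0.666; 1.719 | −0.592; 1.565 |
| v = mean square − mean² | 1.276 | 1.214 |
| Slope of RAI on marker | 0.383/1.025 = 0.37 | 0.364/1.019 = 0.36 |
| Slope of marker on RAI | 0.30 | 0.30 |

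With three comparators per case, v is 1.178 and 1.116, and the slopes are 0.35 and 0.33. If everyone is tested, v = 1 and the bias disappears. If ρ = 0, the slope is 0 whatever v is.

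**2. Overlap of tests.** If testing is local, the pattern is:

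| Center | TMS | VEMPs | BAEPs |
|---|---|---|---|
| Troina (coordinating) | yes | no | no |
| Cagliari | no | yes | no |
| Bologna | no | no | yes |
| San Raffaele | no | no | yes |

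Complete cases for any two of the three tests, or for all three, are 0, whatever the sample size or split. Single-test models do have data: for 500 participants split equally (an assumption) and full uptake, at most 125, 125 and 250. That leaves 75%, 75% and 50% missing.

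**3. Center term.** A model with intercept, one predictor and three center indicators has 5 columns. Its rank is 2 for TMS, 2 for VEMPs and 3 for BAEPs. Center is constant in the first two and has two levels in the third.

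**4. What imputation would supply.** Let two tests never measured together correlate r₁ and r₂ with RAI and r with each other. The joint coefficient of the second is (r₂ − r·r₁)/(1 − r²).

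| Assumed r | r₁ = r₂ = 0.30 | r₁ = 0.30, r₂ = 0.15 |
|---|---|---|
| −0.5 | 0.60 | 0.40 |
| 0 | 0.30 | 0.15 |
| 0.5 | 0.20 | 0.00 |
| 0.8 | 0.17 | −0.25 |

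The data contain no information on r, so the imputation model would choose the row.

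**The case against.** The strongest reply is that the model which cannot be fitted is not in the document. Section 2.11 does not put the three tests into one regression, center is only a candidate covariate, and the outcome in 2.7 is met by one-test models, which have data. This stands. A reader might infer that the planned analysis has no complete cases, or that the third secondary objective must fail. The text does not support either.

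A reader might also infer that unperformed tests will be imputed. Imputation is only something that may be considered, subject to a missing-at-random judgment, and the missing-data pattern is to be reported. What remains is that missingness driven by recorded center could pass that judgment while the association between tests stays unobserved.

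That each test is confined to its center's own recruits is likewise an inference. Section 2.6 says who performs a test, not that only local recruits receive it, and Table 2 has no center limit.

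It may be tempting to add that readers will assume all 85 cases for each test, that the completeness outcome ("Completeness and quality of vPSG, clinical, neurophysiological, and biosample data") will look like failure, or that each test is underpowered. The article sets no completeness denominator, gives no recruitment per center or comparator ratio, and calls these assessments exploratory in section 3. Such details may properly sit in the full plan.

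Finally, sampling by case status does not by itself bias odds ratios, so the logistic model is not open to the selection argument. The linear model is, and none of the replies above answers that.

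**Conclusion.** The point holds in a limited form. The printed linear model takes RAI as outcome while RAI-defined status decides who is tested first, so its slope is biased whenever an association exists. In the worked example it is 0.36–0.37 instead of 0.30, an overstatement of about 19–25%, falling to 0.33–0.35 with three comparators per case and to nothing without an association or with everyone tested.

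The size rests on the normal model, random comparators and full testing of cases. RAI is bounded between 0 and 1, so the actual variance inflation may differ. The comparators for BAEPs are to be matched, which the example does not model.

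Conditional on testing at the recruiting center, joint models across centers have no complete cases, center drops out for TMS and VEMPs, and the association between tests could come only from assumption. The article leaves this route open without committing to it. The analyses are exploratory, so this should be corrected but does not threaten the cohort's main purpose.

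**What to change.** For the neurophysiological markers, replace the sentence in section 2.11 with the following:

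- Fit one model per test, restricted to the center(s) performing it, with the marker as outcome and RAI as exposure. Check linearity in RAI, because the protection against selection depends on that relation being correctly specified.
- Adjust for the covariates listed in 2.11 as far as the sample allows. Include center only for BAEPs.
- Keep these markers out of the pooled regression of RAI on clinical, pharmacological and sleep variables.
- Do not impute tests that were not done by design at other centers.

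Reconcile Table 2 with section 2.6 on which participants are due each test, and say whether testing away from the recruiting center is foreseen.

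The cost is wording. Section 2.12 reports that no results have been generated or analyzed, so the change can still be prespecified. The price is a smaller stated reach for the ancillary analyses, with fewer covariates supportable in each model.

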## 2. Materials and methods

### 2.1. Objectives

The primary objective of DREAMER is to establish a multicenter, harmonized, trial-ready cohort of adults without clinical RBD in whom isolated RSWA can be identified quantitatively by vPSG and followed longitudinally for the development of RBD.

The secondary objectives are:

To estimate the frequency of isolated RSWA in adults aged ≥40 years undergoing laboratory vPSG across participating sleep centers.To compare clinical, sleep, pharmacological, and neurophysiological characteristics between participants with and without isolated RSWA.To evaluate whether quantitative RSWA severity, measured by the REM Atonia Index (RAI), is associated with clinical and instrumental markers potentially relevant to prodromal synucleinopathy.To create a secure, quality-controlled electronic dataset suitable for future long-term phenoconversion analyses.To establish a biobank and multimodal biomarker framework that can support future mechanistic and prevention-oriented studies.

The long-term objective, beyond the 24-month cohort-construction period, is to determine whether baseline isolated RSWA is associated with higher risk of incident RBD and subsequent neurodegenerative outcomes compared with absence of RSWA.

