### 2.5. Baseline assessment

At baseline, all participants will undergo standardized clinical assessment, including demographic characteristics, medical history, neurological history, psychiatric history, cognitive status when clinically indicated, sleep history, history of dream-enactment behavior, sleep-related injuries, parasomnia symptoms, and medication exposure. Particular attention will be paid to antidepressants, dopaminergic medications, benzodiazepines, melatonin, antipsychotics, and other drugs that may influence REM sleep physiology or motor behavior during sleep.

Sleep history will include symptoms of insomnia, excessive daytime sleepiness, obstructive sleep apnea, restless legs syndrome, periodic limb movements, narcolepsy-related symptoms when relevant, and other parasomnias. Standardized RBD screening questionnaires may be used as supportive tools but will not replace clinical and vPSG-based classification.

All participants will undergo full-night laboratory vPSG according to the procedures routinely used in participating centers and harmonized through the DREAMER protocol. Recordings will include electroencephalography, electrooculography, submental electromyography, electrocardiography, respiratory channels, limb electromyography, oxygen saturation, body position, and synchronized video. Sleep staging and respiratory and movement events will be scored according to the current standards adopted by each center and harmonized for the variables included in the DREAMER eCRF.

The key classification variable is RSWA quantified by the RAI. The RAI is an automated measure derived from submental EMG amplitude during REM sleep and has been proposed as part of a practical approach to improve diagnostic accuracy and accessibility in RBD assessment [13]. Values range from 0, indicating complete absence of EMG atonia, to 1, indicating stable EMG atonia [14,15]. The DREAMER protocol adopts the established three-level RAI classification: > 0.9 normal, 0.8–0.9 mildly abnormal, and <0.8 definitely abnormal [14–16]. Participants with RAI < 0.85 and no clinical RBD will be classified as having isolated RSWA, while sensitivity analyses will explore alternative RAI thresholds, including <0.8.

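### Section 2.11 names linear regression for RAI with no provision for unequal variance, so constant-variance intervals may be too narrow for less common exposures that lower RAI (minor)

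*Protocol article*

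**What the plan says.** Section 2.11 gives the model for RAI as a continuous outcome: "Multiple linear regression will evaluate associations between RAI and clinical, pharmacological, sleep, and neurophysiological predictors". The adjustment set is described as follows: "Candidate covariates will include age, sex, antidepressant exposure, neurological comorbidity, sleep apnea severity, REM sleep duration, and participating center". The section mentions no transformation, bounded-outcome model or robust standard error for this regression, and it does not say which standard errors will be used.

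Section 2.5 describes the scale: "Values range from 0, indicating complete absence of EMG atonia, to 1, indicating stable EMG atonia". It grades RAI as "> 0.9 normal, 0.8–0.9 mildly abnormal, and <0.8 definitely abnormal". Section 2.9 expects "approximately 14% of patients without dream-enactment behavior reaching previously established RBD-level RSWA thresholds" and sets the size of the study: "the initial recruitment target is > 500 participants over 18 months, expected to yield approximately 85 individuals with isolated RSWA".

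The regression serves one of the secondary objectives in Section 2.1: "To evaluate whether quantitative RSWA severity, measured by the REM Atonia Index (RAI), is associated with clinical and instrumental markers". It is not the only analysis of RAI. Section 2.11 also says that "RAI will be analyzed both as a continuous variable and as a categorical classification variable", adds logistic regression for isolated RSWA status, and plans sensitivity analyses on antidepressant exposure and on other RAI thresholds.

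**The concern.** In a cohort without RBD, the article's own grading and its expected frequency of about 14% suggest that most RAI values lie just under the upper limit, with a tail of lower values. A variable on 0 to 1 with mean m has variance of at most m(1 − m), and this limit shrinks as m approaches 1. A group close to the limit must be tightly clustered, whereas a group shifted down has room to spread. A factor that lowers RAI can therefore be expected to widen its distribution as well, which conflicts with the constant variance behind the usual standard errors.

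What is at stake is the confidence interval for coefficients such as antidepressant exposure. Section 2.11 puts weight on effect sizes and intervals rather than significance tests, and the Introduction lists medication as one of the competing explanations of isolated RSWA. An interval with the wrong coverage would misstate how precisely that explanation has been measured.

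**Working it through.** The article gives no SD of RAI, no share of antidepressant users and no interval width, so there is no stated figure to reproduce.

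**Inputs from the article:** RAI range 0 to 1; normal above 0.9; about 14% expected with RBD-level RSWA; 500 participants.

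**Assumed inputs:** beta-distributed RAI with precision φ of 10, 20 or 40, the same in both groups; 12% of the unexposed and 25% or 35% of the exposed below 0.85 (14% in both for the no-association case); exposure prevalence p from 10% to 70%. Reading the 14% as the share below 0.85 is itself an assumption, used only to place the distribution.

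**Step 1: spread follows the mean.** For a beta variable, SD² = m(1 − m)/(φ + 1). With φ = 10 and means 0.936 (unexposed) and 0.868 (exposed), the SD ratio is k = √[(0.868 × 0.132)/(0.936 × 0.064)] = 1.38. Across the settings with an effect, k runs from 1.11 to 1.38.

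**Step 2: closed form for a binary predictor.** Up to a common factor:

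- constant-variance formula: V_model = [p k² + (1 − p)] × [1/p + 1/(1 − p)]
- true variance: V_true = k²/p + 1/(1 − p)
- coverage = 2Φ(1.96 × √(V_model/V_true)) − 1

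With k = 1.25:

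| p | V_model | V_true | SE ratio | Coverage |
|---|---|---|---|---|
| 10% | 11.74 | 16.74 | 0.84 | 89.9% |
| 30% | 5.57 | 6.64 | 0.92 | 92.7% |
| 50% | 5.13 | 5.13 | 1.00 | 95.0% |
| 70% | 6.64 | 5.57 | 1.09 | 96.8% |

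The error changes sign at p = 50%. With k = 1 (no association) the two variances are equal at every p.

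**Step 3: simulation.** 500 participants, 2,000 replicates per setting, adjusted for age and sex. The Monte Carlo standard error near 95% is √(0.95 × 0.05/2000), about 0.5 percentage points.

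| Setting | Model SE / true SE | Coverage, constant-variance interval |
|---|---|---|
| Lowers RAI, p = 10% | 0.77–0.90 | 87–92% |
| Lowers RAI, p = 20% | 0.84–0.95 | 90–94% |
| Lowers RAI, p = 30% | 0.87–0.96 | 91–94% |
| Lowers RAI, p = 50% | 0.98–1.02 | 94–96% |
| Lowers RAI, p = 70% | 1.02–1.14 | 95–97% |
| No association, any p | 0.98–1.02 | 94–96% |

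HC3 intervals covered 93–96% in all settings. HC3 is not always the better of the two: with no association, p = 10% and φ = 10 it covered 92.8%, against 94.5% for the constant-variance interval.

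**Step 4: a more dispersed exposed group.** Suppose the unexposed have mean 0.93 and SD 0.07, and the exposed mean 0.86 and SD 0.13. The implied precisions, m(1 − m)/SD² − 1, are 12.3 and 6.1, so this adds dispersion beyond the effect of the ceiling. With k = 0.13/0.07 = 1.86 and p = 10%, the closed form gives V_model = 13.83, V_true = 35.60, an SE ratio of 0.62 and coverage of 78%.

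**Step 5: null predictors correlated with a real one.** With a null predictor present in 50% of the exposed and 15% of the unexposed, false positives at the 5% level are about 5–7% under the constant-variance formula. The highest rate seen, 8.4%, came from settings that include the extra dispersion of Step 4. HC3 gave 4.9–5.4% in those settings.

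**The case against.** The strongest objection is that this is an unstated option and not an error. Section 2.11 names a model class. It does not say that constant-variance standard errors will be used, and linear regression with robust errors is still the model it names. A condensed article often leaves standard errors, residual checks and transformations to a full analysis plan, which is not shown here. This keeps the point minor. It does not remove it, because the outcome's own scale makes unequal variance the expected case, and the same section does provide for the shape of the distribution elsewhere (a rank test as the alternative to the t test).

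A reader might infer that the intervals are too narrow in general. The documents do not support that. They give no exposure prevalence, and the arithmetic reverses above 50% exposure.

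A reader might also infer that spurious predictors would appear. A predictor unrelated to RAI keeps nominal coverage, and one correlated with a real predictor gains only a point or two of false positives in most settings.

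Coverage as low as 78% should not be taken as the expected size either. It needs an exposed group with about half the precision of the unexposed, and nothing in the article indicates that.

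Finally, the secondary objective does not rest on this model alone, since RAI is also analysed by category. That is a partial safeguard: it does not correct the intervals of the linear model, and it replaces graded severity with a cut-off.

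**Conclusion.** The point holds as a minor one. If constant-variance standard errors are used for the RAI regression, intervals for an exposure that lowers RAI and affects 10–30% of participants cover about 87–94% instead of 95%. They are close to nominal at about 50% exposure or with no association, and too wide for majority exposures. Coverage falls below that range only if the exposed group is also more dispersed than the ceiling alone would make it.

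These figures rest on assumed beta distributions, an assumed share below 0.85 and assumed exposure prevalences, none of which the article supplies. That the spread of RAI grows as its mean falls is a reasonable expectation from the bound, but the article does not report it. The analysis serves a secondary objective.

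**What to change.** In Section 2.11, state that the linear regression of RAI uses heteroscedasticity-robust (HC3) standard errors. Optionally, add a fractional-logit model with robust errors as a sensitivity analysis and report average marginal effects, so that results stay on the RAI scale. Preferring that model as the main analysis would be a matter of taste.

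The cost is one phrase and one software setting. Intervals become slightly wider for some predictors, and for a rare exposure with no effect HC3 may cover slightly less than the usual formula (Step 3). Section 2.12 says that no results have yet been generated, so the choice can still be prespecified.
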